## Abstract

**Background:**

In on-pump cardiac surgery, lungs are at high risk of periprocedural organ impairment because of atelectasis formation, ventilator-induced lung injury, and hyperinflammation due to the cardiopulmonary bypass which results in postoperative pulmonary complications in half of this patient population. The new ventilation mode flow-controlled ventilation (FCV) uniquely allows full control of ins- and expiratory airway flows. This approach reduces the mechanical power of invasive ventilation as a possible cause of ventilator-induced lung injury. The scope of FLOWVENTIN HEARTSURG is to compare perioperative individualized FCV with best clinical practice pressure-controlled ventilation (PVC) modes in patients with elective on-pump cardiac surgery procedures. We hypothesize that the postoperative inflammatory response can be reduced by the perioperative application of FCV compared to PCV.

**Methods:**

FLOWVENTIN HEARTSURG is a single-center, randomized, parallel-group trial with two intervention arms: perioperative PCV modes (*n* = 70, PCV group) with an individualized positive end-expiratory pressure (PEEP) and a tidal volume of 6–8 ml/kg predicted bodyweight compared to perioperative FCV (*n* = 70, FCV group) with an individualized PEEP and driving pressure, resulting in a liberal tidal volume. As the primary study endpoint interleukin 8 plasma level is assessed 6 h after cardiopulmonary bypass as a surrogate biomarker of systemic and pulmonary inflammation. As secondary aims clinically relevant patient outcomes are analyzed, e.g., perioperative lung function regarding oxygenation indices, postoperative pulmonary and extra-pulmonary complications, SIRS-free days as well as ICU and total inpatient stays. As additional sub-studies with an exploratory approach perioperative right ventricular function parameters are assessed by echocardiography and perioperative lung aeration by electrical impedance tomography.

**Discussion:**

Current paradigms regarding protective low tidal volume ventilation are consciously left in the FCV intervention group in order to reduce mechanical power as a determinant of ventilator-induced lung injury in this high-risk patient population and procedures. This approach will be compared in a randomized controlled trial with current best clinical practice PCV in FLOWVENTIN HEARTSURG.

**Trial registration:**

German Clinical Trials Register DRKS00018956. Registered on 12 June 2020 (Version 1), last update on 22 August 2022 (Version 4).

**Supplementary Information:**

The online version contains supplementary material available at 10.1186/s13063-023-07201-7.

## Introduction

### Background and rationale {6a}

Invasive ventilation can cause ventilator-induced lung injury (VILI) due to excessive airway pressures, tidal volumes (V_t_), and insufficient positive end-expiratory pressures (PEEP) resulting in barotrauma, volutrauma and/or atelectrauma [1]. Additionally, respiratory rate and airway flows turn into focus as new triggers. All determinants of VILI can be summarized in the mechanical power of invasive ventilation resulting in VILI when applied excessively [2]. The underlying pathophysiological mechanism of mechanical power is called dissipated energy which is applied into the airways during inspiration but not fully recovered during subsequent expiration. This energy is “lost “ in the airways thereby causing lung injury [2, 3].

In conventional mechanical ventilatory modes, inspiration is controlled by pressure (pressure-controlled ventilation, PCV) or volume (volume-controlled ventilation, VCV). In contrast, expiration is driven by the elastic recoil and resistance of the airways/thorax with temporarily high and rapidly changing airway gas flows which cannot be controlled by the operator (Fig. 1). This results in high mechanical power [3].

**Fig. 1 Fig1:**
[figure not shown]
Left column: Course of airway pressures, airway gas flows and ventilated volume during ins- and expiration with conventional PCV (from top to bottom). The relatively abrupt change of airway pressures at the beginning of both ins- and expiration causes a rapid acceleration of airflows into or out of the lungs. The remaining flow profiles during ins- and expiration are characterized by flow deceleration (mid-inspiration and mid-expiration) and eventually end-inspiratory and end-expiratory no-flow phases. Right column: The constant and continuous airway flows during ins- and expiration in FCV (top diagram) effect a linear increase of airway pressures, which are measured in the trachea or at the conventional tube tip when using a conventional tube adapter in FCV (middle). Consequently, ventilated lung volume also increases and decreases linearly during ins- and expiration (bottom)

Since 2017 flow-controlled ventilation (FCV) has been commercially available as a new ventilatory mode (EVONE®, Ventinova Medical B.V., Eindhoven, the Netherlands). With continuous low and constant gas flows during entire ins- and expiration, FCV is the only mode of ventilation in which expiration can be controlled (Fig. 1). This approach reduces mechanical power and dissipated energy of FCV to a minimum in invasive ventilation [3]. In large animal experiments, the application of FCV improved lung function, lung recruitment, homogeneity of ventilation, and reduced lung tissue inflammation in a model of acute respiratory distress syndrome compared to conventional ventilatory modes [4, 5]. Regarding the clinical short-term application of FCV in interventional cross-over studies in lung healthy [6] and obese patients [7], lung function with respect to oxygenation and decarboxylation capacities and regional ventilation distribution were improved compared to conventional volume-controlled ventilation. However, no clinical data exist about the mid-term utilization of FCV in a perioperative context, let alone larger randomized-controlled clinical trials (RCTs). Additionally, even if the theoretical considerations and mathematical models attribute a reduction of mechanical power to FCV [3, 4], clinical data are lacking.

In on-pump cardiac surgery procedures, lungs are not only prone to VILI and periprocedural atelectasis formation. Also, lung ischemia of the alveoli during the cardiopulmonary bypass (CPB) and the consequent lung ischemia/reperfusion injury (LIRI) after CPB termination as well as the extracorporeal circulation itself can cause lung injury which is mediated by hyperinflammation and can manifest at least in temporary organ dysfunction [8].

Every year over one million patients undergo on-pump cardiac surgery procedures worldwide. Due to frequent severe preoperative (pulmonary) comorbidities, invasiveness of the procedures, and the perioperative hyperinflammatory state, cardiac surgery patients are prone to lung injury. Thus, despite fast-track weaning protocols, approximately half of this patient population suffers from some kind of postoperative pulmonary complications (PPCs), ranging from hypoxemia (50%) and pneumonias (below 5%) to the acute respiratory distress syndrome (approximately 1%) [9]. Such postoperative complications extend intensive care unit stays, increase in-hospital mortality, and lead to adverse financial outcomes in health care [10].

As a result, the optimal ventilatory protocol for patients undergoing on-pump cardiac surgery is still under controversial debate. A very recent multicenter RCT (PROVECS trial) could not demonstrate the superiority of a general open-lung concept in various patient-relevant outcomes [9]. Also in non-cardiac surgery, more general and individualized (perioperative) open-lung approaches in large multicenter RCTs (PROVHILO and iPROVE trial) [11, 12] were not convincing in terms of PPCs prevention, even in obese patients (PROBESE trial) [13].

The aim of this trial is to investigate the potential role of individualized FCV as an alternative perioperative ventilation mode in on-pump cardiac surgery procedures and to compare this approach with “best clinical practice” PCV in terms of perioperative inflammation due to VILI, LIRI and invasiveness of the procedure as well as various peri- and postoperative patient-relevant outcomes.

### Objectives {7}

#### Primary objective of the main study

To determine whether perioperative individualized FCV compared to conventional best clinical practice PCV reduces the postoperative inflammatory response due to VILI, LIRI and the cardiac surgery procedure. As the primary endpoint the plasmatic interleukin 8 (IL-8) concentration 6 h after termination of CPB is defined as a surrogate marker of pulmonary and systemic inflammation.

#### Key secondary objectives of the main study

To determine whether FCV compared to PCV benefits the perioperative lung function with respect to oxygenation and decarboxylation capacities, the incidence of PPCs and postoperative extra-pulmonary complications (PEPCs), weaning times from mechanical ventilation and duration of intensive/intermediate care unit stays and time to discharge.

#### Other objectives of exploratory ancillary studies

To determine how an individualized perioperative FCV approach compared to best clinical practice PCV affectsthe perioperative distribution of air within the thoracic cavity. Data are collected by electrical impedance tomography (EIT) before induction of general anesthesia, during pre- and postoperative mechanical ventilation and postoperative spontaneous breathing. Consequently, different EIT-derived parameters will be analyzed (EIT sub-study, see {12}).perioperative right ventricular function. Functional parameters are assessed by perioperative transthoracic (TTE) or transesophageal (TEE) echocardiography prior to induction of general anesthesia under spontaneous breathing as well as before and after CPB (echocardiography sub-study, see {12}). As mechanical ventilation compromises the pre- and afterload of the right ventricle [14], this question arises when considering the contrary intrathoracic pressure course during FCV compared to PCV (Fig. 1). Additionally, in on-pump cardiac surgery procedures, the right heart is also affected by ischemia–reperfusion injury which impacts on echocardiographic right functional parameters itself [15].

### Trial design {8}

FLOWVENTIN HEARTSURG is designed as a randomized, controlled, single-center, superiority trial with two parallel groups. The group assignment will be performed by block randomization with an 1:1 allocation.

In different ancillary studies, the effect of FCV versus PCV on perioperative lung aeration based on EIT-derived data as well as right ventricular, echocardiographic function parameters will be investigated following an exploratory approach.

## Methods: participants, interventions, and outcomes

### Study setting {9}

Potential study participants are all inpatients of the Department for Cardiothoracic Surgery at the BG University Hospital Bergmannsheil Bochum, Ruhr-University Bochum, Germany.

### Eligibility criteria {10}

#### Inclusion criteria

Eligible study participants are aged 18 years or older with a scheduled elective cardiac surgery procedure including conventional CPB and aortic cross-clamping. As scheduled patients are usually admitted on the day before surgery, a minimum of 12 h between obtaining informed consent and induction of general anesthesia is considered as being appropriate.

#### Patient-related exclusion criteria

Suspected or confirmed endocarditis and/or pneumoniaPreoperative (oral) immunosuppressive medicationParticipation in another perioperative interventional trialThe disability to consent independently to study participation.

#### Procedure-related exclusion criteria

Emergency or salvage procedures like in type A aortic dissection or acute myocardial infarctionPatients scheduled for beating heart coronary artery bypass grafting excluding complete aortic cross-clamping, ventricular assist device implantation and heart transplantation.

### Who will take informed consent? {26a}

On the working day before the surgical procedure, the study information will be handed out in paper form to potential candidates after assessing in- and exclusion criteria. The patient is revisited not earlier than after 30 min in order to provide sufficient time to go through the information. Depending on the patient’s specific needs, physicians who are part of the Trial Management Committee (TMC) will explain the study context face-to-face as well as the interventions and perioperative care of each study participant, e.g., additional examinations and the collection of blood samples. Furthermore, the study participants’ rights are communicated, in particular the possibility to terminate study participation at any time without any adverse medical treatment except of the intervention. When all remaining questions have been clarified, the patient can either consent to or deny study participation.

### Additional consent provisions for collection and use of participant data and biological specimens {26b}

Not applicable as the written consent does contain the provisions for the collection and the use of participant data as well as blood samples within the main and ancillary studies specified in the original study protocol.

For future research including analysis of plasma probes, a new votum from a Research Ethics Committee (REC) and additional participant consent must be obtained (see {33}).

## Interventions

### Explanation for the choice of comparators {6b}

Perioperative PCV is a commonly applied mode of invasive ventilation and is preferred to volume-controlled ventilation for some reasons like better patient comfort and lower work of ventilation [16]. Especially for postoperative ventilatory care and ICU patients in need of invasive ventilation, PCV modes like “biphasic positive airway pressure” (BIPAP, Draeger Medical GmbH, Lübeck, Germany) are commonly utilized. Therefore, perioperative PCV with an individual compliance-based best PEEP [12] and driving pressures (DP) ensuring a lung-protective V_t_ of 6–8 ml/kg predicted body weight (PBW) [17] has been chosen for the control group as currently known best clinical practice.

In contrast, perioperative FCV with a compliance-based best PEEP and DP having positive effects on lung function and aeration in pre-clinical mid-term application [4] is utilized in the intervention group.

### Intervention description {11a}

#### General setting

General anesthesia is induced with sufentanil (bolus of 0.3–0.5 μg/kg), propofol (initial bolus of 0.5–1.5 mg/kg following titration depending on the Bispectral index), and pancuronium (bolus of 0.05–0.1 mg/kg) i.v. according to departmental standards. As no volatile anesthetics can be administered technically by the FCV ventilator, total intravenous anesthesia is maintained in both groups by continuous sufentanil (0.5–0.6 μg/kg/h) and propofol infusion (4–6 mg/kg/h) for an intraoperative Bispectral index of 40–50 during the pre- and intraoperative period. During CPB, propofol infusion is suspended and sevoflurane is administered systemically through the membrane oxygenator of the extracorporeal circulation.

After intubation with a conventional tube (ID 8–8.5 mm) and verification of correct tube position by capnometry and auscultation in both groups, patients in the FCV group are additionally equipped with a conventional tube adapter (Ventinova Medical, Eindhoven, the Netherlands). Group-specific invasive ventilation is initiated in a supine position at a PEEP of 5 cm H_2_O and a DP for a V_t_ of 6–8 ml/kg PBW in both groups. PBW is calculated according to PBW = 45.5 + 0.91*(height in cm − 152.4) for female and PBW = 50 + 0.91*(height in cm − 152.4) for male participants.

The respiratory rate in the PCV and airway flows in the FCV group are set to maintain sufficient decarboxylation (arterial pCO_2_ 35–45 mmHg) throughout perioperative mandatory ventilation. Fraction of inspired oxygen (FiO_2_) of the respective respirator is kept in both groups at 0.8 by default throughout the pre- and intraoperative phase.

#### Initial PEEP trial in both groups

In both groups, an incremental PEEP trial follows from 5 to 12 cm H_2_O in 1 cm H_2_O steps with a constant DP which ensures V_t_ of 6–8 ml/kg PBW at the very first PEEP level. As the PEEP trial proceeds, dynamic compliances (C_dyn_) of the respiratory system are calculated [18] and the best PEEP level is defined as the one with the highest C_dyn_ [4, 19]. If patients indicate no hemodynamic instability, for example with the need for passive leg raising, lungs in both groups are ventilated with the compliance-based best PEEP + 1–2 cm H_2_O but ≤ 12 cm H_2_O in order to reduce lung de-recruitment and atelectrauma throughout the pre- and intraoperative phase (Fig. 2) [4, 12, 19]. In the PCV group, the DP is adjusted to maintain a V_t_ of 6–8 ml/kg PBW during the pre-, intra- and postoperative phases until weaning from invasive ventilation (Fig. 2).

**Fig. 2 Fig2:**
[figure not shown]
Brief overview of interventions in the PCV and FCV group with respect to pre- and intraoperative respirator settings. PEEP, positive end-expiratory pressure

#### Secondary driving pressure (DP) trial in the FCV group

In the FCV group, an additional incremental DP trial in 1 cm H_2_O steps is initiated after the PEEP trial. This trial evaluates if the V_t_ increases over-proportional to the C_dyn_ on the previous DP level when the DP is increased by 1 cm H_2_O. As soon as the increase of V_t_ is just proportional, lower, and/or a respiratory rate of 5/min is reached, the DP trial is terminated. In the FCV group patients are ventilated with a DP consistent with the highest C_dyn_ ± 1–2 cm H_2_O during the pre- and intraoperative period [4] (Fig. 2). This approach favors a liberal V_t_ and focuses on a reduction of the respiratory rate and airway flows in order to minimize mechanical power [4].

#### Postoperative respiratory settings

After postoperative admission on the ICU under invasive ventilation, another incremental PEEP trial is conducted in the PCV and PEEP + DP trial in the FCV group in order to individualize group-specific ventilation according to the postoperative condition and the upright patient position of 30–45°. In the ICU, PCV is delivered through the BIPAP modus for patient safety and comfort by default. FiO_2_ is reduced to not less than 0.4 depending on the individual oxygenation capacities.

Patient weaning of invasive ventilation is initiated 3–4 h after CPB end in the case of no new postoperative hemodynamic instability, excessive drainage loss nor gross new pathologies according to the postoperative chest x-ray with the need for intervention. For initiation of weaning continuous propofol infusion is stopped and piritramide (0.1–0.15 mg/kg actual body weight) is administered i.v. If respiratory weaning cannot be commenced due to the above-mentioned criteria, group-specific ventilation will be maintained for up to 24 h after CPB. If the participant still fails extubation by that time, ventilatory settings will be at the discretion of the intensivist in charge and not controlled by study personnel any longer.

PEEP and DP trials, as well as pre- and intraoperative interventions, are all administered and conducted by the same anesthesiologist being in charge of protocol adherence together with a specially trained senior cardiac anesthesiologist.

### Criteria for discontinuing or modifying allocated interventions {11b}

Both in the PCV and FCV group, PEEP levels are allowed to be reduced in 1 cm H_2_O steps and ventilation to be temporarily suspended during internal mammary artery preparation or at any other critical time point depending on the surgeon`s needs in analogy to the PROVECS trial [20]. If the sole reduction of PEEP is not sufficient in the FCV group, the DP might as well be cut down in 1 cm H_2_O steps to an acceptable surgical level. However, PEEP must not fall below 5 cm H_2_O and V_t_ not below 6 ml/kg PBW during the perioperative phase in both groups. The standard application of airway recruitment maneuvers is not intended due to limited clinical benefit and a potentially injurious effect [9]. However, recruitment is mandatory in all procedures with a full aortotomy for deairing the left heart chambers before declamping the ascending aorta. Additionally, recruitment might be unavoidable in case of low oxygenation capacities, especially after CPB termination. Therefore, standardized recruitment maneuvers can be performed at the discretion of the anesthesiologist in charge up to a peak airway pressure of 30 cm H_2_O for a maximum length of 10 s and can be repeated depending on the individual patient needs.

### Strategies to improve adherence to interventions {11c}

The application of ventilatory interventions in both study groups is performed by the same anesthesiologist who is only in charge of protocol adherence. Additionally, all respiratory settings are recorded and documented electronically in an anesthetic report intraoperatively or Patient Data Management System after ICU admission which both can be accessed retrospectively in order to ensure study protocol adherence.

### Relevant concomitant care permitted or prohibited during the trial {11d}

If a participant requires cardiopulmonary resuscitation during the group-specific ventilation, it is mandatory that the ventilation mode is changed to volume-controlled in order to assure a sufficient V_t_. The violation of the designated perioperative ventilation protocol due to this incident or any other operational disturbances for more than 5 min will be reported as an adverse event and is additionally defined as a study stop criterion. As further study stop criteria, we determined more than one cardiopulmonary bypass time and intraoperative death solely due to major surgical complications.

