### Methods in analysis to handle protocol non-adherence and any statistical methods to handle missing data {20c}

In this first larger trial of mid-term FCV application in high-risk cardiac surgery procedures, more than one cardiopulmonary bypass time, intraoperative death, and/or cardiopulmonary resuscitation which are exclusively due to major intraoperative surgical complications as well as study protocol deviations with respect to the allocated intervention for more than 5 min (see {11d}) are defined as stop criteria. It is almost impossible that the perioperative ventilatory mode has an impact on the etiology of these stop criteria, especially as lungs are not being ventilated during CPB in the current study protocol. However, major surgical complications leading to the defined stop criteria and the incidence of the criteria itself significantly affect postoperative patient outcomes. Thus, these patients will be excluded from data analysis whereas all other participant data will be analyzed “as randomized” following an intention-to-treat analysis.

Due to the nature of the intervention and the collection of predominantly short-term data, there will be very few missing data regarding secondary outcomes and (nearly) no missing data with respect to the primary endpoint. Since in most cases these will be due to operational disturbances, loss of paper CRFs, and laboratory errors, missing data can be assumed to be completely missing at random. As the omitting of the (few) missing values will not lead to bias this approach will be utilized for this trial.

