### Adverse event reporting and harms {22}

In the current study protocol PPCs and PEPCs as potential intervention harms with a possible causal relationship are collected after patient enrolment and will be assessed as important clinical secondary outcomes (see {12}). Compound outcome and single PPCs/PEPCs analyses will be performed (see {12} and {20a}).

Intra- or postoperative death is defined as a severe adverse event and will be reported to the local REC. Additionally, all severe adverse events defined as study stop criteria and any protocol violations due to operational disturbances (see {11d}) will be reported and published along with the results of the main study.

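### Adverse-event reporting of a resuscitation during allocated ventilation hangs on a 5-minute adherence limit, and {11d}, {20c} and {22} do not agree on what is reported

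*Protocol article*

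**What the plan says.** Four parts of the protocol article bear on this.

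- **{11d} Concomitant care.** "If a participant requires cardiopulmonary resuscitation during the group-specific ventilation, it is mandatory that the ventilation mode is changed to volume-controlled". The item to be reported is the resulting departure from the ventilation protocol, "due to this incident or any other operational disturbances for more than 5 min will be reported as an adverse event"; the same departure is also a stop criterion. The further stop criteria named there are "more than one cardiopulmonary bypass time and intraoperative death solely due to major surgical complications". Resuscitation attributed to surgery is not among them.
- **{20c} Non-adherence and missing data.** The stop criteria here do include resuscitation, but only "cardiopulmonary resuscitation which are exclusively due to major intraoperative surgical complications", with no limit on duration. In addition, "study protocol deviations with respect to the allocated intervention for more than 5 min (see {11d}) are defined as stop criteria". Patients who meet a stop criterion are left out of the data analysis.
- **{22} Harms.** Any intra- or postoperative death is a severe adverse event. Beyond that, "all severe adverse events defined as study stop criteria and any protocol violations due to operational disturbances (see {11d}) will be reported and published". Pulmonary and extra-pulmonary complications are collected as possible harms of the intervention.
- **{12} Outcomes.** Neither complication list names cardiac arrest, resuscitation or ventilator failure.

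**The concern.** A limit of 5 min is a sensible way to decide whether a patient still received the allocated ventilation. It is a poor way to decide whether something harmful happened. {11d} uses one limit for both purposes, so whether an arrest is recorded as an adverse event depends on how long the ventilator settings differed from the protocol, not on the arrest.

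The limit also appears to work in an unhelpful direction. Resuscitations that the protocol attributes wholly to surgery, and whose cause it considers very unlikely to involve the ventilation mode, count as stop criteria whatever their length. Those with another or an uncertain cause, where a contribution from ventilation cannot be ruled out in advance, have to exceed 5 min.

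This matters more here than in a trial of an established device. The background section says that "no clinical data exist about the mid-term utilization of FCV in a perioperative context", and the discussion calls this the largest randomised trial of flow-controlled ventilation (FCV) so far. Readers will use its harms table. {21a} provides for no data monitoring committee, so the reporting rules carry much of the weight.

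**Working it through.** No figure in the plan bears on this point. The check takes each type of event through each rule.

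**1. What does the 5 min limit in {11d} govern?** The sentence names the resuscitation and then *any other* operational disturbances, followed by the limit. The word *other* places the resuscitation in the same class as the disturbances, which favours reading the limit as covering both. {20c} points the same way: it applies more than 5 min, with a reference to {11d}, to deviations in general. The narrower reading, with the limit attached only to the other disturbances, is grammatically possible.

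**2. Event by event, taking the limit to cover both:**

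| Event during allocated ventilation | {11d} | {20c} | {22} | Lists in {12} |
|---|---|---|---|---|
| Survived arrest, not exclusively surgical, deviation 5 min or less | Not an adverse event | Not a stop criterion | Neither a death nor a stop criterion; covered only if *any* overrides the limit | Not named |
| Survived arrest, exclusively surgical, deviation 5 min or less | Not listed | Stop criterion | Appears reportable as a stop criterion | Not named |
| Arrest of any cause, deviation over 5 min | Adverse event and stop criterion | Stop criterion | Reported | Not named |
| Ventilator or circuit fault, 5 min or less | Not an adverse event | Not a stop criterion | Reported if *any* is taken literally; not if the reference to {11d} brings the limit back | Not named |
| Ventilator or circuit fault, over 5 min | Adverse event and stop criterion | Stop criterion | Reported | Not named |
| Death | Stop criterion only if intraoperative and solely surgical | As {11d} | Always reported | Mortality at 1 and 6 months |

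**3. What the table shows.** The first row is the gap: no rule assures that this event is reported. Set against the second row, the only difference is the presumed cause. The fourth row is a conflict between {11d} and {22}: two staff members could classify the same short fault differently, each with the text on their side.

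**4. A mismatch between lists.** {20c} makes surgical resuscitation a stop criterion and {11d} does not. {22} reports severe adverse events that are stop criteria, so the status of the second row depends on which list is used.

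**5. Denominator.** Because {20c} removes stop-criterion patients from the analysis, a harms table built on the analysis set would lose the reported events too. {22} promises publication of these events but does not name a denominator.

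**The case against.** The case on the other side has substance.

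- *The limit may apply only to other disturbances.* Every resuscitation would then be a reportable violation, since the change of mode is mandatory. This cannot be excluded. The wording of {20c} makes it the less natural reading, and a harm definition should not depend on the parse.
- *{22} says any violation.* This stands, and it defeats the inference that short ventilator faults escape every harm list. Since {11d} seems to class resuscitation among the disturbances, the same word might reach short arrests as well. The cross-reference to {11d} leaves both open, so the supportable statement is that reporting is not assured.
- *Reporting of surgical arrests is itself uncertain.* {22} explicitly names only death as a severe adverse event. A survived surgical arrest is covered only through its status as a stop criterion in {20c}. It is therefore said only to appear reportable.
- *Oversight would catch these events.* A reader might infer that the steering committee would never see them. The documents do not support that: {23} has it review protocol adherence at least every three months, {11c} records all ventilator settings electronically, and {18a} has participants accompanied from intubation to extubation. Seeing an event in an adherence review is still not the same as counting it as a harm.
- *The remaining class is narrow.* Correct. Deaths are reported, and reintubation, hypoxaemia, drained pneumothorax, extracorporeal support and ICU readmission would be captured as complications. Nothing in the documents shows that short events are the ones most likely to be caused by ventilation.
- *The full protocol and case report form may say more.* They may. The point concerns rules that the article does state and that do not fit together, not a missing section.

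**Conclusion.** The point holds in a limited form. On the most natural reading of {11d}, supported by {20c}, a survived arrest that is not judged exclusively surgical and causes a deviation of 5 min or less is not assured of being reported as a harm, while an exclusively surgical one appears reportable whatever its duration. For short ventilator or circuit faults, {11d} and {22} are inconsistent or at best ambiguous. The three sections need reconciling.

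The size cannot be stated as a rate, because the documents give no frequency of arrests or device faults. A reader might reach for the one-sided 95% upper bound for zero events among 70 FCV patients, 1 − 0.05^(1/70) = 4.2%. That figure describes what complete capture of zero events would exclude. It does not measure how many events the rule misses.

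The conclusion rests on two readings: that the 5 min limit governs resuscitation as well as other disturbances, and that the reference to {11d} in {22} may bring that limit with it. If both are wrong, what remains is a need for clearer wording. The primary comparison of interleukin 8 is not affected by this point. It should be changed, but it does not undermine the trial.

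**What to change.** Reconcile {11d}, {20c} and {22}, and separate harm reporting from the adherence rule:

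1. In {11d} and {22}, define every resuscitation during allocated ventilation as an adverse event, regardless of duration and presumed cause.
2. In {22}, state that *any* covers unplanned device- or circuit-related interruptions of allocated ventilation of any duration.
3. Keep the 5 min limit only as a protocol-adherence flag, and use one list of stop criteria in {11d} and {20c}.
4. Tabulate both kinds of event by arm over all randomised patients, including those left out of the data analysis.

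The cost is a reworded paragraph in each section and, if the case report form lacks it, one entry for the event, its duration and presumed cause. Study staff are already present from intubation to extubation, and the electronic ventilator records can be searched for patients already enrolled. The downside is a few more minor events to list. No change to the clinical management of these events is proposed.
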